Importantly, higher levels of homework completion during MFG results in considerably greater effects on child DBD symptoms [19, 20]. As such, skill implementation through homework is an important process for attaining maximal benefits from MFG. Within MFG, homework implementation has been supported through use of multiple empirically supported strategies (e.g., motivational techniques, problem solving barriers to skill implementation, and phone calls between session, as well as home visits [10, 19]). However, despite these significant efforts, rates of homework completion were often poor [19, 20]. The lack of significant benefits of evidence-based approaches used to support the homework implementation process for families engaged in MFG points to a clear need for alternate methods to address this critical issue that attenuates benefits of this intervention approach. Similarly, the considerable efforts that are typically taken to ensure homework implementation poses significant barriers for clinicians in adoption/implementation of MFG. Collectively, greater attention to supporting the homework process has both the potential to enhance clinical effectiveness of evidence-based interventions and to promote greater adoption/implementation of these interventions in clinical practice settings.

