#### Data analyses

Given that the pilot RCT is underpowered to detect differences between groups, our primary analyses will focus on descriptive summary statistics (e.g., means and standard deviation with confidence intervals). Specifically, summary statistics will be compared to established cutoffs on measures. This approach will allow for direct comparison of study summary statistics to established summaries allowing for assessment of various aspects of the DADR homework process (i.e., design, do, and review phases, quality of homework completed). Summary statistics of quantity of homework completed will be directly compared to our previous studies of MFG [9]. Moreover, completion of the measures every session will also allow for determining how each component of the My MFG application is affecting the homework process over time and for identifying key content and processes that may require further development. Collectively, this primary data analytic plan will determine the extent to which the proposed My MFG application affects key aspects of the homework process and allows for gathering of information to further refine the My MFG application.

We will gather information through the feedback questionnaire as well as post-treatment group and individual collaborative consultancy meetings regarding My MFG content, (parents, children, and clinicians) in order to further refine My MFG. We will also utilize My MFG usage data via servers as probes to obtain further information from participants regarding My MFG. The data from these sources will allow us to further understanding patterns of use (e.g., identify patterns of low usage over treatment; identify underutilized content, etc.), consumer challenges (processes, facilitators, and barriers to uptake from participants in using the My MFG application), and allow for further suggestions for refining the My MFG application.

We will also analyze feasibility and effectiveness of the study protocol through ongoing feedback from research staff and MFG facilitators. Information gathered from MFG facilitator/research staff will assist in understanding barriers to implementing the RCT study protocol (i.e., recruitment, retention, facilitator training, and data collection).

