Given the prevalence of DBDs and the limited resources available in outpatient mental health clinics serving disadvantaged communities, maximizing the potential effectiveness and efficiency of existing evidence-based treatments for DBDs, such as MFG, is a high public health priority. We hypothesize that My MFG, which is based on a strong theoretical foundations [9, 31–33], employed through mHealth features via smartphones we have successfully utilized in previous work [34, 35] offers an opportunity to significantly improve the effectiveness of MFG. Importantly, the data gathered through the series of pilot studies described herein allow for a preliminary evaluation and development of the My MFG application. Summary statistics data from the RCT study will inform the extent to which the My MFG application results in high levels of quality and quantity in the homework process and allows for identification of specific content, processes, and/or methods employed in My MFG application that do not appear to result in high rates of quality homework process. The secondary analyses, while underpowered, will allow for detection of a possible “signal” that suggests benefit of My MFG relative to MFG alone. Qualitative feedback from consumers and user data from the My MFG application will augment the session-by-session data. Collectively, the multi-method and multi-informant strategy will allow for further refinement of the my MFG application for potential evaluation in a well-powered subsequent RCT. Lastly, the study RCT will allow us to gauge an important aim—the extent to which the study protocol is feasible and whether and what modifications will need to be made prior to a larger scale evaluation.

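### The primary descriptive plan compares results only with external values, so it cannot show how far My MFG affects homework; effect statements belong to the randomised difference

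*Protocol article*

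**What the plan says.** Under Data analyses, the protocol article gives its reason for a descriptive primary analysis, "Given that the pilot RCT is underpowered to detect differences between groups", and states that "our primary analyses will focus on descriptive summary statistics (e.g., means and standard deviation with confidence intervals". It then names two comparators. For the measures in general, "summary statistics will be compared to established cutoffs on measures". For homework quantity, "Summary statistics of quantity of homework completed will be directly compared to our previous studies of MFG [9". The primary paragraph mentions no comparison with the MFG-alone arm.

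Two conclusions are drawn from this plan. One is that "this primary data analytic plan will determine the extent to which the proposed My MFG application affects key aspects of the homework process". The other is that measuring at every session allows for "determining how each component of the My MFG application is affecting the homework process over time". The main Discussion takes a similar line: "Summary statistics data from the RCT study will inform the extent to which the My MFG application results in high levels" of homework quality and quantity.

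Elsewhere the article is more careful. Primary and secondary aims words the primary aim as obtaining summary statistics, app usage, barriers to uptake and protocol feasibility, and leaves the comparison of arms to secondary analyses. Treatment assignment and sample size rationale describes 1:1 allocation, 40 families per arm, with both conditions running side by side in each clinic. The secondary paragraph of Data analyses plans a between-group analysis and a standardised effect size, and says those results will be treated cautiously because the sample is small.

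**The concern.** To say what the app affects, one needs an estimate of what homework would have been like without it. A cutoff does not supply that, and an earlier study supplies it only if its families, clinics, facilitators, raters, period and homework support match this trial's. The randomised MFG-alone arm supplies it by design. The plan nevertheless attaches its firmest effect wording to the external comparisons, and its only stated caution to the randomised one.

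The component-level statement goes further still. Components are not randomised within the app arm, and which ones a family uses is partly its own choice. Session-by-session ratings can show where use or quality is low. They cannot show what a given component caused.

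At stake is how the pilot's results are described. A high score in the app arm could be reported as something the app produced when the MFG-alone arm scored just as high. A low score could be blamed on the app when both arms were low.

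**Working it through.** **Comparator against conclusion**

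| Statement in the protocol article | Comparator | What it can support |
|---|---|---|
| Primary: process and quality measures | Established cutoffs | The level reached |
| Primary: homework quantity | Earlier MFG studies | The level, relative to another sample |
| Primary: each component over time | None stated | A description of patterns |
| Secondary: between-group analysis and effect size | Concurrent randomised MFG alone | An effect of adding the app |

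The effect wording in the primary paragraph rests on the first three rows. Only the fourth supports it.

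**Inputs.** 40 families per arm (Treatment assignment and sample size rationale). An 80% retention target (Primary and secondary aims), which gives 0.80 × 40 = 32 per arm if losses are even. Six to eight families per group (Multiple family group). The article gives no SDs or benchmark values, so everything is in SD units. The background shifts, the intraclass correlation (ICC) and a group size of 7 are assumptions. No figure in the article is contradicted, and none bears on this point that could be reproduced.

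**Step 1: how easily a background shift passes for an effect.** Suppose the app does nothing, but this trial's families differ from the benchmark by b SD for other reasons. The probability that one arm's 95% interval lies wholly above the benchmark is 1 − Φ(1.96 − b√n). At n = 40 and b = 0.3: b√n = 0.3 × 6.325 = 1.897, and 1 − Φ(0.063) = 0.475.

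| Assumed shift (SD) | n = 40 | n = 32 |
|---|---|---|
| 0 | 0.025 | 0.025 |
| 0.1 | 0.09 | 0.08 |
| 0.2 | 0.24 | 0.20 |
| 0.3 | 0.48 | 0.40 |
| 0.5 | 0.89 | 0.81 |

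These figures ignore grouping. A shift common to both arms cancels in the difference MFG plus My MFG minus MFG alone.

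**Step 2: what the randomised estimate costs in precision** (95% half-widths, n = 40 per arm).

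- One arm: t(0.975, 39)/√40 = 2.023/6.325 = 0.32 SD.
- Between arms, no grouping: 1.96 × √(2/40) = 0.44 SD (0.49 SD at 32 per arm).
- Between arms, with groups of 7 in both arms: design effect 1 + 6 × ICC, which is 1.3 at ICC 0.05 and 1.6 at ICC 0.10.
  - Normal critical value: 1.96 × √(2 × 1.3/40) = 0.50 and 1.96 × √(2 × 1.6/40) = 0.55 SD.
  - t critical value: 80/7 gives roughly 12 groups, so about 10 degrees of freedom and a value of 2.228. Half-widths are 2.228 × 0.255 = 0.57 and 2.228 × 0.283 = 0.63 SD.

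The one-arm figure carries no design effect. Like for like, the between-arm interval is wider by about √2.

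**Step 3: does low power justify the external comparison?** Power at 40 per arm, ignoring grouping, is 0.27 for a difference of 0.3 SD, 0.61 for 0.5 SD and 0.95 for 0.8 SD. About 0.63 SD is needed for 80% power. The article's description of the trial as underpowered is fair for small to moderate effects. That is a reason to report an estimate with its interval instead of relying on a test. It is not a reason to draw the effect conclusion from an uncontrolled comparison.

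**The case against.** The strongest reply is that this is loose wording in an otherwise sound pilot plan, and much of that stands.

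- **The control arm is not ignored.** A reader might infer that the trial sets it aside. It does not. The secondary analyses compare the arms on homework quantity, quality and process, and compute a standardised effect size. The main Discussion ties any benefit relative to MFG alone to those analyses.
- **A descriptive primary analysis is not a fault.** It fits a pilot and matches the stated primary aim. Nothing here calls for a primary hypothesis test.
- **Levels and contrasts are partly separated already.** The hypotheses first say ratings will be high and then, separately, that they will exceed those under MFG alone.
- **The next trial does not hang on the historical comparison.** A reader might infer that it does. The article states no go/no-go rule based on it, and it draws on feasibility, feedback, usage and the between-arm signal.
- **A change in homework support is not stated.** Multiple family groups for DBDs says that support in MFG has included "phone calls between session, as well as home visits". A reader might infer that this was withdrawn here and that the benchmark is therefore unlike. The intervention descriptions do not say so. Comparability is unestablished, but a difference is not shown.
- **The summaries may cover both arms.** The primary paragraph does not restrict them to the app arm. Even so, the only comparators it names are external.

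What survives is that the primary paragraph claims an effect, overall and by component, that its comparators cannot deliver and that the primary aim does not ask for.

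**Conclusion.** The concern holds for the conclusion attached to the primary analysis, not for the choice of a descriptive analysis. Comparison with cutoffs and earlier studies can describe levels. It cannot determine what My MFG affects, still less what each component does. The contrast that can support such a statement is already planned as a secondary analysis.

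The size of any resulting error cannot be known from the article. The probabilities of 0.24 to 0.89 for shifts of 0.2 to 0.5 SD at n = 40 show sensitivity under assumed shifts; they do not show that such a shift exists. The clustered half-widths likewise rest on an assumed ICC and group size. The logical point depends on none of these figures.

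This should be corrected because the change is cheap and removes an avoidable source of bias from the trial's effect statements. It does not undermine the design.

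**What to change.** 1. In the primary paragraph of Data analyses, limit the conclusion to levels, usage and feasibility, in line with the stated primary aim.
2. Base any statement about what My MFG affects on the randomised difference, MFG plus My MFG minus MFG alone, with a 95% interval that allows for the treatment groups. State the direction, because the effect-size sentence as worded subtracts the app arm from MFG alone.
3. Show both arms beside the cutoffs and the earlier MFG results, labelled as context only.
4. Drop the component-level effect claim, or call it exploratory and describe it as patterns of use and ratings.
5. Reword the corresponding sentence in the main Discussion.

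The cost is rewording in two places and one between-arm column in the primary table. No new data are needed, and the article reports that the data were still being coded, cleaned and analysed. The drawback is the wider interval shown in the working, which should be reported as it stands.

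A separate editorial check: reference [9], given for the earlier MFG studies, is elsewhere the source for the homework framework and rating scales, while MFG results are cited as [19, 20]. This is not part of the point.

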### Interventions

#### Multiple family group

Multiple family group (MFG) is a 16-week service delivery strategy that was guided by a manualized protocol. Each group included six to eight families, composed of identified youth, their adult caregiver(s), and sibling(s) between the ages of 6 and 18. As a foundation, MFG takes a common elements approach by identifying essential components from the empirical literature regarding core effective practices for treating DBDs, represented as the 4Rs (i.e., rules; responsibility; relationships; respectful communication) and factors related to family engagement in mental health services, represented as 2Ss (stress and social support. Each of the 16 sessions that focused on one of the 4Rs and 2Ss and proceeded with the following processes: (a) creating social networks; (b) information exchange/homework review; (c) group discussion regarding the skill; (d) individual family practice; and (e) homework assignment.

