#### Measures

Data will be collected at baseline, pretreatment, at each session, and at post-treatment. See Table 1 for the data collection tools and timing of the collection of each measure. My MFG usage data (e.g., frequency, duration of use, which components used, etc.) will also be collected directly from servers throughout treatment.

**Table 1 Tab1:** Outcome measures for pilot randomised controlled trial phase

Domain	Measure	Reporter	Time of assessment
Homework process; homework quantity and quality	Homework rating scale-II [9]	Parent and clinician	Every session
Homework process	Homework adherence and competence scales [9]	Independent observer	Every session
Attendance	Session attendance	Clinician	Every session
Consumer satisfaction and feedback	Treatment attitude inventory [40] Feedback questionnaire Group and individual consultancy meeting	Parent; target child; therapist	Postreatment

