Secondary analyses will focus on between group (group: MFG plus My MFG and MFG-alone) X 2 (time: pre-treatment and post-treatment) repeated measures multivariate analysis of variance (MANOVA) to address homework quantity and quality at each session, average homework quantity and quality across all sessions, and quality of the design, do, and review processes. Alpha-inflation correction procedures will not be used for subsequent contrasts given the exploratory nature of the study. Follow-up analyses will include calculation of effect size by subtracting the MFG plus My MFG group mean from the MFG-alone group mean and dividing by the pooled standard deviation of the groups. Effect size data will be an important indicator of a “signal” that My MFG may be improving the homework process given the relatively small sample size of this study. Independent sample *t* tests will be used for determining differences between treatment conditions on consumer satisfaction to treatment. It is important to state that the results of these secondary analyses will be treated with caution given the small sample size of the RCT.

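### The secondary homework analysis uses a pre-treatment/post-treatment time factor that the session-only homework data cannot supply

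*Protocol article*

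**What the plan says.** The secondary analyses (Data analyses) cross the two arms with a two-level time factor, written as "X 2 (time: pre-treatment and post-treatment) repeated measures multivariate analysis of variance (MANOVA) to address homework quantity and quality at each session". The same sentence extends the model to "average homework quantity and quality across all sessions, and quality of the design, do, and review processes".

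The Measures section opens with a general statement: "Data will be collected at baseline, pretreatment, at each session, and at post-treatment". For the timing of individual measures it defers to the table: "See Table 1 for the data collection tools and timing of the collection of each measure". In Table 1 the Homework Rating Scale-II (parent and clinician) and the homework adherence and competence scales (independent observer) are both collected at every session. Attendance is also collected at every session. Satisfaction and feedback is the only post-treatment row, and satisfaction is analysed by t test. No row is placed at baseline or pretreatment.

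The primary-analysis text also treats homework as session-level data, in a sentence that runs in part "completion of the measures every session will also allow for determining how each component of the My MFG application is affecting the homework process over". The description of MFG lists the steps of each of its 16 sessions, ending with "d) individual family practice; and (e) homework assignment".

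**The concern.** A pre/post factor needs each outcome to be observed before and after treatment. The homework outcomes are observed during treatment, session by session. Before the first session there is no MFG homework to rate, and no design, do or review process either. The sentence also conflicts with itself: it puts a two-occasion factor on outcomes defined at each session, and on averages that reduce to one number per family.

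This is the only inferential model named for the between-arm parts of hypotheses 1 to 3. Those hypotheses concern a difference in level during treatment, not a change from before treatment. An analyst who cannot fit the stated model has to improvise. The choice of sessions and contrast is then open after the data are in, with no multiplicity correction planned.

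**Working it through.** **1. Schedule against model**

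| Outcome in the MANOVA | Collected (Table 1) | Pre-treatment value? |
|---|---|---|
| Homework quantity and quality | every session | none |
| Design, do and review quality | every session | none |
| Average over all sessions | derived, one value per family | none; no time dimension |

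**2. Estimability**

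The group x time model has four parameters: intercept b0, group bG, time bT and group x time bGT. Take the most favourable reading and treat the session ratings as the post level. Only two cell means are then observed:

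- MFG alone: b0 + bT
- MFG plus My MFG: b0 + bG + bT + bGT

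Two equations cannot determine four unknowns, and a numerical check gives a design matrix of rank 2. The arm difference, bG + bGT, can be estimated. The time and group x time terms cannot.

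**3. If early and late sessions were substituted**

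The article does not propose this. We assume session 1 stands for pre and session 16 for post, because it is the most obvious way to force the model. In the app arm the homework process runs through My MFG and no delayed start is described, so session 1 falls after randomisation and may already carry the effect.

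Assumptions, none of them given in the article: SD sigma = 1, equal correlation rho between any two sessions, two-sided alpha 0.05, a constant benefit of 0.5 SD, complete data and independent families (clustering by MFG group ignored). From the article: 40 families per arm and 16 sessions.

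- Group x time: expected effect 0.5 - 0.5 = 0, so power equals alpha. Simulated rejection (4,000 runs per correlation) was 5.2%, 5.3% and 4.7% at rho = 0.3, 0.5 and 0.7.
- Group main effect, from the mean of two sessions: variance sigma^2(1 + rho)/2. At rho = 0.5 this is 1.5/2 = 0.75 sigma^2.
- Mean of 16 sessions: variance sigma^2[rho + (1 - rho)/16]. At rho = 0.5 this is 0.5 + 0.5/16 = 0.531 sigma^2.

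The last two are the like-for-like comparison, because both estimate the arm difference in level.

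Power with 40 per arm (normal approximation):

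| rho | Group x time, constant effect | Group main effect, 2 sessions | 16-session average |
|---|---|---|---|
| 0.3 | 5% | 79.2% | 96.8% |
| 0.5 | 5% | 73.3% | 86.6% |
| 0.7 | 5% | 67.9% | 75.1% |

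If the effect instead grew from 0.25 to 0.5 SD, group x time power would be 15.7%, 20.1% and 30.3%. At the 80% retention target (0.8 x 40 = 32 per arm), the 16-session average has 92.7%, 78.3% and 65.5%. All these powers are illustrative. The article states no alpha, power, effect size or SD, so there is no planned figure to reproduce.

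**The case against.** Four points can be made for the plan.

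- **The general statement names pretreatment collection.** This does not help. Table 1 is given as the timing of each measure and places no homework instrument there, and MFG homework does not exist at that point.
- **A between-arm estimate survives without the MANOVA.** This stands. The same section specifies an effect size, the difference in group means over the pooled SD, and calls it an important indicator of benefit. It has no time term and can be computed from session ratings or their average, although the text does not say which. A reader might infer that the plan leaves no usable between-arm homework comparison; the document does not support that.
- **A forced model would not test the wrong effect throughout.** This also stands. Only group x time misses a constant benefit. The group main effect still compares the arms, and the article does not say which term is the test of interest. Nor does the article discard sessions: the two-session version is our construct, and its own text names outcomes that use all sessions.
- **The analyses are exploratory.** The article calls the pilot underpowered, makes descriptive summaries primary and says the secondary results will be treated with caution. This limits the harm but does not make the stated model fit the stated data.

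**Conclusion.** The stated model does not match the stated data. No homework outcome has a pre-treatment value, so time and group x time cannot be estimated, and the session average has no time factor. That conclusion rests only on the article's own schedule and its description of MFG. It is a fault in a rule that the article states, not a detail left to an analysis plan.

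The size of the consequence depends on assumptions. Under a forced first/last-session model with a constant effect, group x time has no power beyond alpha. The group main effect remains valid but less precise than the session average: 0.75 against about 0.53 sigma^2 at an assumed correlation of 0.5.

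A reader might take this to invalidate the trial's main results. It does not: usage, barriers, summary statistics and protocol feasibility are untouched. The fault is confined to the exploratory secondary tests of hypotheses 1 to 3, and it should be fixed on that footing.

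**What to change.** Delete the pre-treatment/post-treatment factor from the secondary analysis. Compare the arms on the session-averaged homework scores that the section already names, and report the difference with a 95% CI.

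Alternatively, fit a mixed model to the session ratings with arm, session and arm x session and a random intercept for family. Take the arm difference averaged over sessions as the main contrast and arm x session as the time course. With complete data and equal weight per session, the two routes estimate the same difference. With missed sessions they can differ, so name one as the main analysis. Base the effect size on the same average.

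No new data are needed, since the ratings are already scheduled at every session. It is still more than a change of wording: Current status of the study says the trial was recently completed and its data are being coded, cleaned and analyzed. The new analysis should therefore be dated and reported as a change made after data collection.

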#### Social support services (relatedness)

##### *Discussion groups*

Participants can exchange emotional support and information with others assigned to their MFG group via online support groups. They can share their progress in achieving My MFG goals and ask questions of both group participants and facilitators.

All of the tools that will be included lay self-determination theory over the DADR model of homework implementation, providing tools that motivate and engage, improve competence, or provide social support for the client during the critical do process. Tools can be customized during the design phase of the homework process and modified during the review phase of the homework process during the MFG group. The game can be adaptive to families via simple initial tasks and leveling-up to more difficult tasks that are related to more difficult to adopt behaviors.

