#### Treatment assignment and sample size rationale

Families will be assigned on a 1:1 basis to MFG alone (*n* = 40) or MFG plus My MFG (*n* = 40) (see Fig. 2 CONSORT flowchart) via predetermined sequence based on random permutation calculation by the project director, who is blind to family information. Both treatment conditions will run in parallel within each participating clinic. Sample size will be determined based on previous randomized controlled trial data suggesting that a sample size of 40 participants per condition would provide a meaningful difference in homework completion between those that are typically highly engaged and those that are less engaged.

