#### Multiple family group plus MY MFG

MFG plus MY MFG treatment condition has the same format, content, processes, and methods as MFG except that the homework process (homework review/homework assignment) is conducted through the My MFG application.

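### Families are treated in MFG groups in both arms, but the secondary MANOVA and t tests take them as independent, so p-values can be too small

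*Protocol article*

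**What the plan says.** The unit of randomisation is the family: "Families will be assigned on a 1:1 basis to MFG alone" or to MFG plus the app, with 40 per arm (Treatment assignment and sample size rationale). Treatment is then given in groups. Under Multiple family group the article states "Each group included six to eight families", over 16 sessions that include group discussion. The app arm keeps this structure: "MFG plus MY MFG treatment condition has the same format, content, processes, and methods as MFG", apart from the homework process. It also adds contact inside the group: "Participants can exchange emotional support and information with others assigned to their MFG group via online support groups" (Discussion groups). Both arms run side by side in every clinic.

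Under Data analyses, the secondary between-arm comparison is an arm-by-time "repeated measures multivariate analysis of variance (MANOVA) to address homework quantity and quality at each session, average homework quantity and quality across all sessions" and the quality of the design, do and review processes. For satisfaction, independent-sample t "tests will be used for determining differences between treatment conditions on consumer satisfaction to treatment". The primary analysis is "descriptive summary statistics (e.g., means and standard deviation with confidence intervals"; how the intervals are calculated is not stated. The article mentions no group, facilitator or clinic effect, no ICC and no design effect. Its only stated reason for caution about the secondary results is the small sample.

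**The concern.** Families in the same MFG group share sessions, discussion and peers, and in the app arm an online forum as well. Building support between members is part of the intervention, so some correlation of outcomes within a group is to be expected. A two-arm MANOVA and an independent-sample t test have no place for it. They count 40 separate pieces of information per arm when there may be fewer.

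The stated caution about small numbers does not cover this. A small sample makes a test weak, whereas ignored grouping makes it too ready to declare a difference. The protocol hypothesises significantly better results in the app arm on several outcomes, plans no correction for multiple contrasts, and looks to the secondary analyses for a signal in favour of a larger trial. A p-value or standard error that ignores groups would make that signal look firmer than it is.

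**Working it through.** **Inputs from the protocol article.** 40 families per arm; groups of m = 6 to 8 families in both arms; retention target 80%, so 0.80 × 40 = 32 per arm. The ICC is not given; 0.01 to 0.20 is an assumption.

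**The plan's own figure.** The sample size rationale says only that "a sample size of 40 participants per condition would provide a meaningful difference in homework completion" between more and less engaged families. It gives no alpha, power, effect size or standard deviation, so 40 cannot be reproduced. For reference, with independent families, two-sided alpha 0.05 and 80% power, the detectable standardised difference is (1.960 + 0.842) × √(2/40) = 0.63.

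**Number of groups.** 40/8 = 5 and 40/6 = 6.7, so about 5 to 7 per arm.

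**Design effect.** DE = 1 + (m − 1) × ICC. The true standard error is √DE times the one that ignores groups, and the effective number of families per arm is 40/DE. Example: m = 7 and ICC 0.10 give DE = 1 + 6 × 0.10 = 1.60, √1.60 = 1.26 and 40/1.60 = 25.

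**False-positive rate.** Simulated under no treatment difference, 20,000 trials per setting, two-sample t test at nominal 5%, no clinic effect:

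| Assumed ICC | DE, m = 6 to 8 | SE ratio √DE | Effective families per arm | 5 groups of 8 | 6 groups of 6-7 | 32 retained, 5 groups |
|---|---|---|---|---|---|---|
| 0 | 1 | 1 | 40 | 5.0% | 5.0% | 5.0% |
| 0.01 | 1.05-1.07 | 1.02-1.03 | 37-38 | 5.8% | 5.6% | 5.5% |
| 0.05 | 1.25-1.35 | 1.12-1.16 | 30-32 | 9.4% | 8.4% | 8.1% |
| 0.10 | 1.50-1.70 | 1.22-1.30 | 24-27 | 13.3% | 11.6% | 11.5% |
| 0.20 | 2.00-2.40 | 1.41-1.55 | 17-20 | 21.6% | 18.1% | 18.2% |

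A t test on group means stayed between 4.7% and 5.3% in all these settings. The MANOVA itself was not simulated; its between-arm terms rest on the same assumption of independent families.

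**Clinic effect.** Arms are crossed with clinic, so clinic variation cancels from the arm difference but stays in the error term. With 5 groups of 8 per arm, one per clinic, the t test that ignores groups gave:

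- 4.0% with clinic ICC 0.10 and group ICC 0
- 5.8% with clinic ICC 0.10 and group ICC 0.02
- 8.6% with clinic and group ICC both 0.05 (9.4% without the clinic effect)

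Inflation therefore needs a group component beyond clinic. In the same three settings a group-mean t test without clinic was conservative (1.6%, 1.8% and 3.2%), which is a reason to keep clinic in the model.

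**Arm means.** If ordinary 95% intervals were used for the primary summaries, with 5 groups of 8 and no clinic effect they would cover about 94%, 91%, 87% and 79% of the time at ICC 0.01, 0.05, 0.10 and 0.20.

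**The case against.** The other side has a fair case. The trial is called underpowered, description is primary, the tests are labelled exploratory and to be read with caution, and no decision rule rests on a p-value. The signal is read from the standardised effect size, a point estimate that grouping does not bias. The harm depends on an ICC that nobody has stated, and at 0.01 it is slight. All of this stands. It lowers the weight of the point, but it does not make the named tests fit the design. Nor is this a detail left to a fuller plan, because the article states the methods.

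Some stronger readings are tempting but not supported:

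- **That the primary confidence intervals ignore groups.** The article gives no interval method, so the coverage figures above are conditional. What can be asked is that any such intervals allow for group.
- **That false-positive rates are certainly too high.** They can be. It depends on correlation within groups, and clinic variation can offset part of it.
- **That the correct degrees of freedom are 8 to 12.** That is 2 × (5 − 1) to 2 × (7 − 1), with no clinic term. The number of clinics is not stated. If five clinics each ran one group per arm, 10 groups less one intercept, one arm term and four clinic terms would leave 4.
- **That therapist-rated satisfaction has only as many independent raters as groups.** The article does not say how facilitators are allocated or whether they rate once or per family.

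**Conclusion.** The point holds for the secondary between-arm analyses. Families are randomised singly and treated in about 5 to 7 groups per arm, while the MANOVA and t tests carry no group term. With no clinic effect, the true false-positive rate of a nominal 5% test is about 6% at ICC 0.01, 8-9% at 0.05, 12-13% at 0.10 and 18-22% at 0.20. These rates rest on assumed ICCs, equal in both arms, and on a t test of a single outcome. A group correlation close to zero, or clinic variation that outweighs it, would leave little or no inflation. The effect-size estimate is unaffected; what is overstated is its precision and the strength of the p-values. Because the tests are secondary and exploratory, this should be fixed but is not critical.

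**What to change.** Analyse every between-arm comparison, satisfaction included, with a random effect for MFG group in both arms, clinic as a factor and small-sample degrees of freedom. Satterthwaite and Kenward-Roger are both acceptable. A simpler alternative is an analysis of group means, preferably with clinic kept in. State that any confidence intervals for arm means in the primary summaries allow for group membership. Report the ICC of each outcome with its interval. With 10 to 14 groups it will be imprecise, so it is rough input for the later trial and not a firm basis for its sample size.

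The cost is a few lines of analysis text and model code. Group membership is known from delivery and no new data are needed. The article describes the pilot trial data as still being coded, cleaned and analysed, so at that point the change can still be made. The price is wider intervals and fewer degrees of freedom, how many depending on the number of clinics and groups actually run.
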